## Attention

### *Attention as a potential mechanism to explain deficits in motor learning in DCD*

Attention is critical for skill acquisition, with mild or moderate impairments impacting learning efficacy (Boyd, Vidoni, Siengsukon, & Wessel, 2009). Three to four different types of attention have been defined in the literature: orienting, selective, divided and sustained (Fortenbaugh, DeGutis, & Esterman, 2017; Posner, 1990; Raz, 2004). Sustained attention is particularly important when learning has to occur in an invariant, relatively predictable context as in the learning of the rVMA task. A child does not need to divide, select or differently orient its attention when confronted with a computer screen and joystick to control a marker going to predetermined target positions, whether congruently or in a rotated fashion. On the contrary, sustain attention is critical since learning this task requires many practice trials which follow relatively fast. A small break in the maintenance of attention to the task will have large error consequences. In addition, limited capacity to sustain attention may hinder the formation of an internal model necessary to consolidate the task. Important attention related information can be obtained by examining multiples measures of behavior such as the reaction time which has been shown to be highly sensitive to changes in sustained attention (Derosière, Dalhoumi, Perrey, Dray, & Ward, 2014; Fortenbaugh et al., 2017).

A particularly sensitive period of development for sustained attention capacity seems to be between 6 to 9 years of age. Betts, Mckay, Maruff, and Anderson (2006) investigated sustained attention in children with TD between 5 and 12 years of age. They diagnosed a rapid development from 5-6 years to 8-9 years and a developmental plateau from 8-9 years to 11-12 years. Whether this developmental trajectory is the same for children with DCD is not known, but it places a target age range to examine issues of attentional development in children with DCD.

Children with DCD have more attentional problems than their peers (Dewey et al., 2002). Specifically, Fong et al. (2016) found that children with DCD were less attentive to M-ABC movements than their peers, even when subjects with comorbid ADHD were eliminated. These authors used a one-channel electro-encephalography (EEG) placed over the prefrontal cortex (PFC) to assess attention (Fong et al., 2015) showing that the attention index was significantly associated to M-ABC motor impairment so poor motor performance was explained by inattention after controlling for age, sex, body mass index and physical activity level.

It seems that different brain activation measurement techniques, such as EEG and functional magnetic resonance imaging (fMRI), could assist in elucidating group differences in attention. For instance, the dorsolateral prefrontal cortex (DLPFC) has been linked, together with anterior cingulate, to attentional control (Fassbender et al., 2004; Milham, Banich, Claus, & Cohen, 2003). Using fMRI and performance on an attention inhibition task, Querne et al. (2008) have suggested that children with DCD (without ADHD) may have a dysfunction in the attentional

brain network, as evidenced by less prefrontal activity compared to controls during a “go/no-go” task. Also, Zwicker et al. (2011) found lower levels of blood oxygen-level dependent (BOLD) signal in DLPFC in a trail tracking task (learning and retention). Similarly, Debrabant et al. (2013), using fMRI and a sequence learning task with predicted or unpredicted interstimulus intervals found that DCD children showed less activation than typically developing children in the right DLPFC. Together, these results suggest that poorer attentional capability may be one factor that impacts motor skill acquisition in children with DCD and neuroimaging can help elucidate these differences. However, whether these differences are also mediated by the visuomotor integration network in children with DCD has not been examined.

Although EEG and fMRI are techniques widely used, optical technologies provides a less invasive and more practical way to examine brain activation in pediatric populations (Buss, Fox, Boas, & Spencer, 2014; Imai et al., 2014; Lloyd-Fox, Blasi, & Elwell, 2010; Lloyd-Fox, Wu, Richards, Elwell, & Johnson, 2015; Nishiyori, Bisconti, Meehan, & Ulrich, 2016; Vanderwert & Nelson, 2014). Functional near infrared spectroscopy (fNIRS) technique uses light to measure changes in cerebral oxygenation and deoxygenation fractions of hemoglobin ( $[O_2Hb]$  and  $[HHb]$ , respectively). It has been used in adults to reliably determine different levels of brain activity in different conditions, including activity of regions related to sustained attention (Derosière et al., 2014) (Figure 3). Similarly, fNIRS has been used in pediatric populations such as children with and without disabilities to examine attention and executive function (response inhibition, cognitive shifting, working memory, and attention) (for a review see, Moriguchi & Hiraki (2013). Reliability of the fNIRS as measures of brain activation in children has been proven (Blasi, Lloyd-Fox, Johnson, & Elwell, 2014). Recently, Caçola, Getchell, Srinivasan, Alexandrakis, & Liu (2018) used fNIRS to examine cortical activation in children with DCD performing different tasks (finger tapping, curve tracing, and paragraph writing). DCD children compared to TD children showed different focal activation patterns, even for the finger tapping (a simple task with no spatial or temporal demands), and these differences were also task-specific (for example, differences in the right DLPFC were found for the paragraph writing).

|  |                                                                                              |
|--|----------------------------------------------------------------------------------------------|
|  | 
Figure 3. Near Infrared Spectroscopy (NIRS) pilot data during the execution of
 |
|--|----------------------------------------------------------------------------------------------|

[figure not shown]

#### Attention: Exercise as an enhancer of learning via attention

Although the specific underlying mechanisms by which physical exercise can improve learning and memory are not clear, several proposals have been placed forward. At the molecular level, and as mentioned before, changes in the concentrations of catecholamines (e.g. norepinephrine; T. McMorris, Collard, Corbett, Dicks, & Swain, 2008) and neurotrophic factors

(e.g. brain derived neurotrophic factor, BDNF; Koehl et al., 2008; Schwarz & Kindermann, 1990; Winter et al., 2007) have been shown to be related to the enhancement of learning when exercise is implemented. Alternatively, two psycho-cognitive factors, arousal and attention, may also mediate the relationship between physical exercise and improved learning. An optimal level of arousal is necessary to effectively use the limited attention capacity (Kahneman, 1973). This effective use of attention, in turn, facilitates learning (Catroppa & Anderson, 1999).

It is, therefore, plausible that moderate acute physical exercise places the individual at the appropriate level of arousal (not too high, not too low) and assists in the maintenance of attention, so the learning and consolidation of a new motor-perceptual task, like the rVMA task, are improved. In fact, Medina et al. (2010) found that the attention deficits in children with ADHD could be minimized via physical exercise using an acute interval exercise of 30 minutes and assessing sustained attention using the Conner's Continuous Performance II test. However, these authors had no measurements of learning or memory. Furthermore, no studies have examined the effect of acute exercise on the attention capacity of children with DCD and whether sustained attention plays a role in the exercise-induced enhancement of learning.

## **JUSTIFICATION AND HYPOTHESES**

This project is designed to provide a multidisciplinary link between the educational sciences, sports sciences, and neurosciences to better understand a relevant population of children suffering from DCD. Results from this project have translational applications to teachers, parents, and other children educators that will allow them to elaborate adequate interventions from solid evidence (i.e., science-based interventions). In addition, innovative key-enabling technologies use will ensure that the knowledge generated will go after the next frontier in education and neuroscience field. The key concept is the emerging idea that physical exercise is the “new preventive medicine” for chronic vascular and metabolic diseases, but also it has been shown to be an enhancer of learning, even as a result of an acute bout of exercise. Children are at a developmental phase where the brain is still very plastic and establishment of enduring healthy habits is more effective. Children with DCD have problems with learning motor skills which are the support for a long-lasting active life style, and becoming physically active adult individuals. Unfortunately, therapeutic interventions are not main stream for this population despite its high prevalence (6%).

Motor learning entails integration of motor and sensory information and is constraint by our capacity to sustain attention. It is suggested that difficulties to perform motor tasks by children with DCD are related to poor visuomotor integration and attention deficits. Our previous work suggested that improvements learning a motor skill are related to experience in exercise and sport (Busquets, Marina, & Angulo-[name], 2013; Busquets, Marina, Iruetia, Ranz, & Angulo-[name], 2011; Ferrer-[name] et al., 2018) even when learners suffer some disorder or functional incapacity (R. M. Angulo-[name] et al., 2017; R. M. R. Angulo-[name], Peirano, Algarin, Kaciroti, & Lozoff, 2013; Valentín-Gudiol et al., 2017). Furthermore, results from our studies (R. Angulo-[name] et al., 2019; Ferrer-[name] et al., 2018; Ferrer-[name], Busquets, Lopez-Alonso, Fernandez-del-Olmo, & Angulo-[name], 2017) have demonstrated that acute intense exercise enhances motor learning in adults and children with typical development. However, whether children with DCD could benefit from this strategy to improve their motor learning capacity is not known. The scarce brain studies conducted with adults about the exercise-learning interaction (Dal Maso, Desormeau, Boudrias, & Roig, 2018) indicate that acute exercise benefits on motor learning may be associated, in part, to changes in the brain activity. However, no similar studies in children, much less in DCD children, have been published thus far. Therefore, concurrent brain imaging and behavioral assessments would be the next logical step to explore the exercise benefits on learning in children with or without DCD.

In order to examine the combined effect of acute exercise and learning on children's brain activity, widely used neuroimaging techniques are either too expensive, or do not allow for in-situ assessment (i.e., same location where learning is occurring, in our case, children's school). Optical technologies have been utilized and suggested as potential and promising tools to fully study the alterations of the brain networks. Perhaps most importantly, the features of the new technological approach (non-invasive, quantitative, safe, inexpensive and portable) and the characterization of brain activity using fNIRS will allow us to conduct studies in-situ (i.e., children's school) with robust results, including estimation of what brain areas are more or less activated while learning in children with DCD. In addition, combination of two optical techniques, fNIRS and DCS, has the potential to add new reliable information of the children's brain activity during learning which open the door to conduct a pilot study to verify this potential. This knowledge is hypothesized to assist in the design of better, more targeted interventions. In addition, exercise benefits in learning, if confirmed in this population, could also be integrated as part of effective educational interventions for children with DCD. Our research hypotheses are arranged around these concepts.

- H1: Children with DCD will show worse motor learning (slower movements, more variability, slower rate of learning, and worse consolidation) than

typically develop (TD) children when facing a rotational visuomotor adaptation task (rVMA). Performing an acute intense exercise bout before rVMA will improve consolidation in TD and DCD children. In addition, exercise will narrow the gap between children with DCD and children with TD. Based on the null exercise effect on adaptation previously found in TD children, we have no predictions for DCD children.

- H2: Cortical activation measured by fNIRS from the visuomotor integration and the attentional network areas during the baseline phase will be lower in the children with DCD than in children with TD. Relative activation levels ( $[O_2Hb]$ ) in both networks during adaptation and consolidation will demonstrate opposite profiles in children with DCD (start low, end high) vs children with TD (start high and end low). In addition, acute intense exercise will narrow, but may not completely close, the gap between children with DCD who receive the exercise intervention and children with TD controls.
- H3: In a pilot study, combining fDCS technology that measures  $CMRO_2$  and rCBF with fNIRS technology will provide us with the possibility to obtain more accurate and robust information of the children's brain activity during learning than using fNIRS alone.

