## **OBJECTIVES**

Although the long term objective of this line of research will address the underlying mechanisms of acute exercise effects on motor learning and possible brain activity changes with developmental coordination disorder (DCD), we currently defined the specific objectives of this project as follows:

- O1. To study the acute intense exercise effects on the motor learning (adaptation and consolidation) in children with and without DCD from a behavioral perspective (performance and execution).
  - O1.1- Characterize the possible motor learning modulators (physical fitness; physical activity level; attentional and cognitive capabilities) in children with and without DCD.
  - O1.2- Compare the motor learning (adaptation and consolidation) ability of children with and without DCD while performing a rotational visuo-motor task (rVMA) (CON-DCD vs. CON-TD).
  - O1.3- Examine the effect of acute intense exercise on motor learning (adaptation and consolidation) while performing a rotational visuo-motor task in children with and without DCD.
- O2. To explore cortical activation in the visuomotor integration and the attentional network areas while learning a motor adaptation task in children with and without DCD under rest or post-exercise conditions. Visuomotor integration and attentional network areas will include dorsolateral pre-frontal cortex (DLPFC), ventrolateral pre-frontal cortex (VLPFC), and oculo pre-frontal cortex (OPFC).
  - O2.1- Assess changes in cortical activation ([O2Hb]) during rVMA learning (adaptation and consolidation) in children typically developed and in children with DCD.
  - O2.2- Evaluate the impact of acute intense exercise on changes in cortical activation ([O2Hb]) during rVMA learning (adaptation and consolidation) in children typically developed and in children with DCD.
  - O2.3- Associate the presence of changes in the cortical activation variables with differences shown in behavioral variables.
- O3: To explore via a pilot study the combined use of two optical neuroimaging techniques (fNIRS and fDCS) to measure cortical activation in the visuomotor integration and the attentional network areas while learning a motor adaptation task in children with and without DCD under rest or post-exercise conditions.
  - O3.1- Evaluate the usability of the hybrid device

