At the start of session 2, participants will be familiarized with the rVMA protocol (familiarization set) by performing 20 trials of non-rotated ( $0^\circ$ ) practice trials. Afterwards, a non-rotated baseline condition set (104 trials) will be performed. After the baseline set, the EX groups (i.e., EX-DCD and EX-TD) will perform a 13-min iE session while the CON groups (i.e., CON-DCD and CON-TD) will rest the same period of time reading or holding a conversation, no additional exercise or musical activity will be permitted. Next, all participants will do an adaptation set (312 trials) in the rVMA task, with a clockwise rotation of  $60^\circ$  applied to the cardinal coordinates of the cursor movement. At one hour after the end of the adaptation set, all participants will perform a  $60^\circ$  clockwise retention set (short-term retention, RT1h, 104 trials). At the end of session 2, all participants will perform a memory game with the cards they collected during the 20mSRT and potentially the iE.

Sessions 3 and 4 will occur 24 h and 7 days from the end of the adaptation set. In each session, participants will perform a  $60^\circ$  clockwise rotated retention set (mid and long term retentions, RT24h, and RT7d respectively, 104 trials each).

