$$y = a * e^{b*x} - c * e^{d*x}$$

where  $y$  is the error (epoch's mean),  $x$  is the epoch number and  $a$ ,  $b$ ,  $c$  and  $d$  are parameters. The initial rate of learning (RL) will be computed, as described in Coats (2014), as the first derivative of the first half of the function and evaluated at epoch 1 for both error variables IDE (RL-IDE) and RMSE (RL-RMSE). All individual exponential functions will be visually inspected for a plateau to assess that learning is achieved.

Progress towards increasingly skilled performance consists of the acquisition and stabilization of more effective movement patterns (Vereijken, Van Emmerik, Bongardt, Beek, & Newell, 1997). Inter-trial variability could be used to assess the stabilization level of the task. High values of variability are related to an early learning stage that explores new solutions for the task while low values of variability are associated with more skilled performers showing stable executions. Changes in variability across epochs in the acquisition set (i.e., rate of variability, RV) for both error variables (RV-IDE-SD and RV-RMSE-SD) will be also computed.

Normalized changes in concentration levels of hemodynamic variables during the different sets will be analyzed. Neural activation of each cortical area will be expressed as an increase of  $[O_2Hb]$  (also of  $CMRO_2$  and CBF in the pilot study) and a decrease in  $[HHb]$  (Mandrick et al., 2013). Qualitative analysis of the changes in these variables across trials will be performed to establish differences in hemodynamic patterns. Average and SD of the hemodynamic variables for each set will be calculated.

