We will compare the mean baseline value for each rVMA and brain hemodynamics variables with ANOVAs to evaluate baseline performance across the four groups. Differences between the CON-DCD and CON-TD children groups (O1.2 and O2.1) on the motor learning (adaptation and retention phases) will be explored using independent t-tests in the adaptation set, while 2 (Group) x 3 (Time) ANOVAs with repeated measures will be used to analyze differences in the retention phases. Focusing on the effects of exercise (O1.3 and O2.2), possible differences in the adaptation set will be contrasted by 2 (Group) x 2 (Exercise) ANOVAs and retention tests will be analyzed by 2 (Group) x 2 (Exercise) x 3 (Time) ANOVAs with repeated measures. Association of the changes in brain activation variables with changes occurred in the rVMA variables will be explored using bivariate correlations and multivariate correlations (O2.3). Usability and additional information provided by fNIRS and fDCS will be evaluated qualitatively and contrasted brain activity levels obtained from both technologies using t-test and ANOVAs (adaptation: t-test (Technology); retention tests: 2 (Technology) x 3 (Time) ANOVAs) (O3).

Before any statistical test normality distribution will be tested for all variables via exploration of histograms, Q-Q plots and with the Shapiro-Wilk's normality test. When the normality assumption failed, variable transformation or non-parametric alternative tests will be adequately conducted. In all ANOVAs Greenhouse-Geisser sphericity-corrected values will be used when appropriate. Variables with initial group differences and significantly correlated with the dependent variable will be considered as potential covariates in the ANOVA analyses. Bonferroni *post hoc* analyses will be performed if significant differences are found. In addition, the effect size will be calculated using  $\eta^2p$  (0.01 small, 0.06 medium, 0.14 large effect). Statistical significance was set at  $p < 0.05$  for all analyses.

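### The profile part of H2 is a Group x Time prediction, but [O2Hb] in the adaptation set is tested without a Time factor and kept out of the retention model

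*Protocol*

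**What the plan says.** Protocol, Justification and Hypotheses, H2, on relative [O2Hb] in the two cortical networks while the task is learned and retained: it "will demonstrate opposite profiles in children with DCD (start low, end high) vs children with TD (start high and end low"). H2 has two other parts: lower activation in DCD at baseline, and a narrowing of the DCD-TD gap by exercise.

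Protocol, Objectives, O2.1: "Assess changes in cortical activation" during learning, covering adaptation and consolidation.

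Protocol, Variables, gives the quantitative summaries of the optical signal: "Average and SD of the hemodynamic variables for each set will be calculated". The course over trials is handled descriptively: "Qualitative analysis of the changes in these variables across trials will be performed to establish differences in hemodynamic patterns".

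Protocol, Statistical analysis, names the tests. For CON-DCD against CON-TD (O1.2 and O2.1), differences "will be explored using independent t-tests in the adaptation set, while 2 (Group) x 3 (Time) ANOVAs with repeated measures will be used" for the retention phases. For exercise (O1.3 and O2.2), "possible differences in the adaptation set will be contrasted by 2 (Group) x 2 (Exercise) ANOVAs". Exercise effects on retention go to a Group x Exercise x Time ANOVA with three time levels, which are the retention tests at 1 h, 24 h and 7 days.

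**The concern.** Opposite profiles are a statement about how the group difference changes over time. A test of that statement needs at least two time points from the relevant period in one model. In the adaptation set the plan offers one value per child and no Time factor. The adaptation set also never shares a model with the retention sets, so a change from adaptation into retention has no test either.

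At stake is the most specific imaging prediction in the protocol. Children with DCD could follow the predicted course and the adaptation test could miss it. Conversely, a significant adaptation test could be reported in support of H2 when it shows only that one group was higher on average. The direct evidence on the profile would be a qualitative description of traces.

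**Working it through.** **What each planned analysis can show**

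| Analysis | Time factor | Can it show opposite profiles? |
|---|---|---|
| Adaptation, O2.1: t-test | none | No, only a level difference |
| Adaptation, O2.2: 2 x 2 ANOVA | none | No, only level differences |
| Retention: repeated-measures ANOVAs | RT1h, RT24h, RT7d | Only across retention sets |
| Course across trials | descriptive | No inferential statistic |

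The SD per set does not help: it has no sign, so a rise and an equal fall give the same value. The 8-trial epochs (312/8 = 39) are introduced in the rVMA paragraph of Data reduction, and the rate of learning in Variables is defined only for the two error variables. Neither is carried into an fNIRS test.

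**Size of the loss.** The protocol gives no effect size or power for the fNIRS profile, so there is no stated figure to reproduce.

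Input from the protocol (Participants): 30 per group in CON-DCD against CON-TD, alpha 0.05. Assumed: two-sided testing; early and late half-set means with SD 1; within-child correlation r of 0.3 to 0.7; the t-test applied to the set average. The sizes 0.55 and 0.78 are borrowed from the protocol's behavioural sample-size paragraph; all other sizes are chosen for illustration.

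Let the DCD-minus-TD difference be d1 early and d2 late.

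- Set mean: difference (d1 + d2)/2, SD sqrt((1 + r)/2).
- Late minus early, which is the Group x Time interaction for two time points: difference d2 - d1, SD sqrt(2(1 - r)).

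Symmetric crossing, d1 = -0.4, d2 = +0.4, r = 0.5:

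- Set mean: (-0.4 + 0.4)/2 = 0, so power equals alpha, 5%.
- Interaction: 0.8/sqrt(2 x 0.5) = 0.8 SD, power 86%. It is 73% at r = 0.3 and 98% at r = 0.7.

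Converging profile, d1 = -0.8, d2 = 0, r = 0.5:

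- Set mean: absolute difference 0.4, SD sqrt(0.75) = 0.866, standardised 0.46, power 42%.
- Interaction: again 0.8 SD, power 86%.

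All cases, as ranges over r = 0.3 to 0.7:

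| Early / late difference (SD) | Set-mean test | Early/late interaction |
|---|---|---|
| -0.40 / +0.40 | 5% | 73-98% |
| -0.55 / +0.55 | 5% | 94% to >99.9% |
| -0.78 / +0.78 | 5% | >99% |
| -0.55 / +0.78 | 8% | 99% to >99.9% |
| -0.40 / +0.78 | 12-14% | 97% to >99.9% |
| -0.20 / +0.78 | 23-28% | 88% to >99% |
| -0.80 / 0 | 38-47% | 73-98% |
| -1.00 / +0.20 | 38-47% | 97% to >99.9% |

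The set-mean test responds only to the net imbalance. Its power is 5% only for exact symmetry, about 8% close to symmetry, and roughly 12-47% for the clearly asymmetric or converging cases.

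**The case against.** A reader might infer that H2 as a whole is untested, or that the planned analysis must return a null when H2 is true. The protocol does not support either.

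- **Start and end are not defined.** H2 speaks of adaptation and consolidation and does not place the crossing inside the adaptation set. If start means adaptation and end means late retention, the adaptation mean is the start value. The t-test then addresses whether DCD starts low, with power at 30 per group of 55% for 0.55 SD and 84% for 0.78 SD. The retention ANOVA addresses group level and divergence afterwards. This stands. What remains missing on that reading is a test of the change from adaptation to retention, because two separate models do not provide one.
- **The 5% depends on exact symmetry**, which H2 does not state. This stands, and the table shows the rest of the range.
- **Only one part of H2 is affected.** Baseline activation has its ANOVA and the exercise effect is addressed by the Group x Exercise models. O2 is also framed as exploratory, and a qualitative analysis across trials is declared. All true, but a directional prediction still needs a statistic that can show it.
- **The t-test's dependent variable is inferred.** Statistical analysis does not say that the hemodynamic t-test uses the set average, and such detail may sit in an analysis plan not shown here. However, the average and SD per set are the only quantitative summaries defined for these variables, and any single value in a two-group test leaves out Time unless it is itself a change score. No such score is defined.

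**Conclusion.** The point holds for the profile part of H2. As written, no planned inferential test can show opposite [O2Hb] profiles within adaptation or from adaptation to retention. The cost ranges from complete loss (power equal to alpha) for a symmetric crossing within adaptation to partial loss (roughly 12-47% power) for asymmetric or converging profiles. Even a significant adaptation test would establish a net level difference and not a profile.

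These figures rest on assumed effect sizes and correlations, a crossing or convergence inside the adaptation set, and use of the set average. The mismatch between hypothesis and model does not depend on the power figures. It should be corrected before analysis; the baseline and exercise parts of H2 can stand.

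**What to change.** In Variables and Statistical analysis:

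1. Summarise [O2Hb] per cortical area in consecutive adaptation blocks: three blocks of 104 trials (3 x 104 = 312, the length of the baseline and retention sets), or early against late.
2. Test Group x Block for O2.1 and Group x Exercise x Block for O2.2, and name that interaction as the test of the profile part of H2.
3. State whether start and end mean within adaptation or adaptation to retention. If the latter, add a Group x Phase contrast of late adaptation against RT24h and RT7d. An equally spaced linear trend from early adaptation to RT7d would be unsound, since the steps run from minutes to 7 days.
4. If RT1h enters any cross-phase comparison, specify its normalisation. Data reduction normalises to the resting reference, but the optical neuroimaging section lists no rest recording before RT1h.

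The cost is small. The fNIRS signal is sampled at 10 Hz throughout the sets, so no new data or visits are needed. The price is one more repeated factor and noisier block means than set means.
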